### Objectives

The aim of our trial is to compare the efficacy of the recommended SIS technique utilizing a conventional parallel approach against the end-on approach for RFN of the CMBN in patients presenting with chronic, moderate-to-severe, neck pain in the context of cervical facet joint disease. The following are the primary objectives of this trial:To compare the difference in mean Numerical Rating Scale (NRS) for pain scores at 3 months after the study interventions.To compare the proportion of patients with a positive analgesic response (defined as 50% or greater reduction in the NRS score for neck pain as compared to baseline) at 3 months after the study interventions.

The following are the secondary objectives:To compare the difference in mean NRS for pain scores at 1, 6, and 12 months after the study interventions.To compare the proportion of patients with a positive analgesic response at 1, 6, and 12 months after the study interventions.To compare the proportion of patients with 10 points or greater reduction in the Neck Disability Index (NDI) score (the minimal clinically important difference (MCID) [8]) at 1, 3, 6, and 12 months after the study interventions.To compare the proportion of participants reporting some or much improvement in the Patients’ Global Impression of Change (PGIC) scale at 1, 3, 6, and 12 months after the study interventions [9].To compare the mean Pittsburgh Sleep Quality Index (PSQI) scores and EuroQol (EQ-5D-5L) scores at 1, 3, 6, and 12 months after the study interventions [10].To compare the duration of performing the study interventions, patient discomfort, radiation dose, and cost of the study interventions.To compare average physical activity and sleep duration as measured by wrist-worn actigraphy over 1 week before the procedure and 1-month follow-up after the study interventions.To assess the incidence of peri-procedural complications and post-procedural adverse effects during and at 1, 3, 6, and 12 months after the study interventions.To assess opioid requirements in daily oral morphine equivalents in milligrams averaged over the 1 week prior to the 1-, 3-, 6-, and 12-month follow-ups after the study interventions.To assess the patient assumption of the group they were assigned to at 3-month follow-up after the study interventions.

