**Inclusion criteria**
1. Age 18 to 85 years
2. Predominant axial (non-radicular) neck pain for at least 3 months
3. 7-day average NRS score for neck pain of 5/10 or greater at baseline evaluation
4. Moderate or greater functional impairment due to pain, defined as NDI Questionnaire raw score of 15 out of 50 (30%) or greater
5. Failure to respond to conservative medical management (pharmacologic, physical therapy) for at least 3 months. 6. Positive response to two consecutive diagnostic blocks of the CMBN with a short and long-acting anesthetic, respectively, defined as reporting at least 80% relief of index pain concordant with the expected duration of the local anesthetics

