The following are the *secondary outcomes*:Pain intensity: The between-group difference in mean NRS for pain intensity scores at 1, 6, and 12 months after the interventions.Incidence of analgesic response: The between-group difference in the proportion of patients with a positive analgesic response (defined as 50% or greater reduction in the NRS score for neck pain as compared to baseline) at 1, 6, and 12 months after the interventions.Neck pain-related disability: The between-group difference in the proportion of patients with a 10% or greater reduction in the Neck Disability Index (NDI) score at 1, 3, 6, and 12 months after the interventions.Participant-assessed improvement: The between-group difference in the proportion of participants reporting some or much improvement on the Patients’ Global Impression of Change (PGIC) scale at 1, 3, 6, and 12 months after the interventions.Quality of sleep and life: The between-group difference in the mean Pittsburgh Sleep Quality Index (PSQI) scores and EuroQol (EQ-5D-5L) scores at 1, 3, 6, and 12 months after the interventions. Sleep health will be assessed using PSQI, and actigraphy-measured variables respectively, including sleep duration, sleep quality, daytime sleepiness, sleep timing, and wakefulness after sleep onset.Procedure-related outcomes: The between-group difference in the duration of procedure, discomfort, radiation dose, and cost of the procedures.Actigraphy-collected physical activity and sleep: The between-group difference in the average physical activity and sleep duration as measured by wrist-worn actigraphy over 1 week prior to the procedure and 1 week prior to the 1-month follow-up after the interventions.Adverse effects of the interventions: The between-group difference in the incidence of peri-procedural complications and post-procedural adverse effects at 1, 3, 6, and 12 months after the interventions.Analgesic requirements: The between-group difference in opioid requirements as measured by daily oral morphine equivalents in milligrams averaged over the 1 week prior to the 1, 3, 6, and 12 months follow-ups after the interventions.The patient assumption of the group they were assigned to at 3-month follow-up after the study interventions

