### Sample size

The sample size was calculated using the Statistical Package for the Social Sciences (SPSS, IBM SPSS Statistics) software. A sample size of 72 participants (36 in each treatment group) will provide 80% power to detect a difference (inferiority margin), at 3 months after the intervention, in the mean NRS pain intensity scores (0–10 scale) between the two treatment groups being less than or equal to 1 point, given a standard deviation (SD) of 1.7 at the 0.05 significance level (alpha) using a two-sided two independent sample *t*-test. To satisfy both the non-inferiority and superiority hypothesis, we plan to recruit a total of 80 participants to account for a presumed 10% dropout rate. The sample size calculations and the assumptions underlying it are based on data published on RFN of nerves supplying other axial joints (lumbar facets, sacroiliac) for the relief of spinal pain [12, 13]. The chosen non-inferiority margin of less than or equal to 1 point (10%) is reasonable because a minimal clinically important difference in pain scores for a treatment to be considered efficacious is 2 points or 30% [14]. A non-inferiority study is justified to compare the end-on and parallel RFN lesions because similar efficacy is expected but there may be a lower incidence of adverse effects (e.g., patient discomfort) and better resource utilization (e.g., faster procedure time, lower radiation dose) with the end-on RFN technique.

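### The secondary NDI responder outcome has two unreconciled thresholds, 10 points in the objectives and 10% in the outcomes, with neither the scale nor the base stated

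*Protocol article*

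**What the plan says.** The protocol article mentions an NDI threshold in three places.

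- **Objectives (secondary).** The groups are to be compared on the proportion of patients with a "10 points or greater reduction in the Neck Disability Index (NDI) score" at 1, 3, 6 and 12 months. The text calls this the MCID and cites a source for it.
- **Outcomes (secondary).** The neck disability item is "The between-group difference in the proportion of patients with a 10% or greater reduction in the Neck Disability Index (NDI) score", at the same four visits.
- **Table 1, inclusion criteria.** Entry requires at least moderate impairment, "defined as NDI Questionnaire raw score of 15 out of 50 (30%) or greater". This is the only place where the article gives a scale for the NDI.

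Two other places show how the article uses percentages. The pain responder in the Outcomes section is "defined as 50% or greater reduction in the NRS score for neck pain as compared to baseline", so that percentage is relative to the patient's own starting score. The Sample size section says of the pain margin: "The chosen non-inferiority margin of less than or equal to 1 point (10%) is reasonable". There the percentage is a share of the 0-10 scale.

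**The concern.** One outcome at one set of visits should have one cut-off. Here the objective gives it in points and the outcome definition in percent, and nothing in the article links the two. Each is also incomplete by itself: the points lack a scale and the percentage lacks a base.

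At stake is whether the NDI responder result is fixed in advance. This responder proportion is the only NDI quantity in the secondary outcomes list, and the Hypotheses section includes function among the domains for which non-inferiority is hypothesised. As written, an analyst could apply either threshold and cite the protocol for it. On several readings the two would sort some patients differently.

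**Working it through.** **Inputs**

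- Raw NDI maximum 50 and lowest eligible baseline 15 (Table 1). The one NDI conversion in the article reproduces: 15 / 50 = 0.30, the stated 30%.
- Objectives threshold: 10 points, scale not stated.
- Outcomes threshold: 10%, base not stated.

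**Thresholds in raw points**, for a patient with raw baseline B between 15 and 50:

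- 10 points on the raw scale: 10.
- 10 points on the 0-100 scale: 10 × 50 / 100 = 5.
- 10% of baseline: 0.10 × B.
- 10% of the full scale: 0.10 × 50 = 5.

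**Ratio of the objectives threshold to the outcomes threshold under each pair of readings**

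| Baseline B | 10% of B (raw points) | Raw points vs 10% of baseline: 10 / (0.10 B) | 0-100 points vs 10% of baseline: 5 / (0.10 B) | Raw points vs 10% of scale: 10 / 5 | 0-100 points vs 10% of scale: 5 / 5 |
|---|---|---|---|---|---|
| 15 | 1.5 | 6.67 | 3.33 | 2.0 | 1.0 |
| 20 | 2.0 | 5.00 | 2.50 | 2.0 | 1.0 |
| 25 | 2.5 | 4.00 | 2.00 | 2.0 | 1.0 |
| 30 | 3.0 | 3.33 | 1.67 | 2.0 | 1.0 |
| 50 | 5.0 | 2.00 | 1.00 | 2.0 | 1.0 |

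The thresholds agree for every patient on one of the four pairs only: 0-100 points with percent of the full scale. If points are raw, they differ at least twofold at every eligible baseline.

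The 6.67 at baseline 15 is an upper bound. If scores are whole numbers, the smallest fall of at least 1.5 points is 2, and the ratio there is 10 / 2 = 5.

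**One patient.** Take a fall from 20 to 17 raw points, a drop of 3.

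- Outcomes rule, percent of baseline: 3 / 20 = 15%, which is at least 10%. Responder.
- Objectives rule, raw points: 3 is less than 10. Not a responder.
- Objectives rule, 0-100 points: 3 × 100 / 50 = 6, less than 10. Not a responder.
- Outcomes rule, percent of full scale: 3 / 50 = 6%, less than 10%. Not a responder.

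So the conflict for this patient does not depend on the scale of the points. It depends on the percentage being relative to baseline.

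**The case against.** The strongest reply is that the two statements may mean the same thing. If the points are on the 0-100 scale and the percentage is of the full scale, both are 5 raw points and no patient is classified differently. The text gives this some support. Table 1 expresses a raw score as a share of the maximum, the pain margin is expressed the same way, and the NDI item, unlike the pain responder, does not say that the reduction is relative to baseline.

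This stands as far as it goes: a reader might infer that the two rules must classify patients differently, and the article does not establish that. But the harmonising reading needs two unstated assumptions. The pain responder in the same list uses a percentage the other way, and Table 1 states the entry score as a raw score out of 50, so the 0-100 scale is not an obvious default for points. The text therefore remains unreconciled even if the authors meant one rule.

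Two other inferences are tempting and unsupported.

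- A reader might conclude that a 10% relative cut-off lies within measurement error, so that nearly all patients would respond in both arms and a real difference would be hidden. The article gives no NDI measurement error and no expected distribution of NDI change, so this cannot be shown from it.
- A reader might treat this as the trial's main measure of function. The article lists it as one of several secondary outcomes, and its assessment schedule (Table 2) assigns physical functioning to actigraphy.

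It is also fair to say that the Statistical methods section already plans differences with 95% confidence intervals for secondary outcome scores, so the NDI result need not rest on the cut-off alone.

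**Conclusion.** The point holds as an unreconciled definition of one secondary outcome. The size of the gap depends on the reading: a ratio of 1.0 if both statements refer to the 0-100 scale, 2.0 for raw points against percent of scale, and 2.0 to 6.7 for raw points against percent of baseline. The top figure applies only at the lowest eligible score and should not be read as typical.

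The calculation rests on the raw 0-50 scale and the entry minimum of 15 in Table 1, and on no outside figure. How many trial patients would change category cannot be calculated, because the article gives no distribution of NDI scores.

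The consequence is limited. The sample size rests on the pain score, and both primary outcomes are defined on the pain score, so neither changes. The correction should still be made, because a responder cut-off left open until the data are seen is not prespecified.

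**What to change.** Before unblinding, state one threshold in both the Objectives and the Outcomes sections, with its scale (raw 0-50 or 0-100) and, if a percentage is kept, its base. The 10-point reduction is the only rule for which the protocol gives a reason, so it should replace the 10% in the secondary outcomes list. The scale should be the one on which the cited MCID source expresses its points. The authors need to check this, since the article does not say.

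Optionally, name the between-group difference in mean NDI, with its 95% confidence interval, among the secondary outcomes. This would make explicit what the Statistical methods section already implies.

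The cost is a sentence in each place. The NDI is already collected at every follow-up visit, so no new data are needed.

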## Abstract

**Background:**

Cervical facet joint disease is a common source of neck pain and its prevalence increases with aging. Conservative multimodal management options (e.g., strengthening of neck muscles, non-steroidal anti-inflammatory medications, massage, and thermal modalities) often fail to relieve pain. Cervical medial branch nerve (CMBN) radiofrequency neurotomy (RFN) is an effective minimally invasive technique for treating chronic neck pain secondary to facet joint disease. An end-on approach for this procedure has been proposed that may be technically easier and require less time while reducing post-procedural discomfort. The protocol presented here is for a study that aims to compare the efficacy of a new end-on approach using multi-tined cannulae, against the conventional parallel technique that employs straight cannulae for RFN of the CMBN in patients with chronic neck pain due to cervical facet joint disease.

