## Introduction

### Background and rationale

Parallel radiofrequency neurotomy (RFN) of the cervical medial branch nerves (CMBN) utilizing sharp straight needles was first demonstrated to be clinically efficacious in a randomized clinical trial (RCT) setting for the treatment of chronic neck pain following whiplash injury almost three decades ago [1]. Over the next 20 years, several other studies followed with variable success rates. In the early 2000s, in a consecutive series of cases, the authors reported a success rate (defined as the complete abolition of pain) of 46 and 26% following RFN of the CMBN at 6 and 12 months, respectively [2]. Previously, an observational study in the late 1990s had already reported a success rate (defined as abolition of pain) of 57 and 36% at the 6- and 12-month follow-up, respectively [3]. Later, in 2012, a study conducted in New Zealand reported a success rate (defined as greater than 80% pain relief) of 68 and 51% at 6 and 12 months post-procedurally, respectively [4]. In addition, the rate of complications between studies also showed variability throughout the years. The rates of temporary post-procedural dysesthesias have been noted to vary from 43 to 67%, while the rates of temporary cutaneous numbness have been reported to range between 36 and 58%. Of note, only the rates of post-procedural pain seem to be relatively concordant between authors, with reported rates varying between 95 and 100% among studies. This data was comprehensively analyzed in a systematic review published in the late 2010s by the Standards Division of the Spine Intervention Society (SIS), where the authors looked at the effectiveness and risks of fluoroscopically guided parallel (also called conventional) RFN of the CMBN [5].

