#### Post-procedural management

Following completion of the procedure, participants will be taken to the post-procedure recovery unit. Any complications related to the procedure will be recorded and managed if required. Participants will be discharged from the unit as per routine hospital policy. As per standard of care, participants will be advised to take one to two tablets of Percocet (containing 5 mg of oxycodone and 325 mg of acetaminophen) or Tylenol number 3 (containing 30 mg of codeine and 325 mg of acetaminophen) every 6 h if required to a maximum of 8 tablets in 24 h if they have pain intensity NRS scores higher than 3 out of 10. Frequency of use of these medications by study participants will be recorded and the average daily opioid consumption in oral morphine equivalents for the 1 week preceding the follow-ups at 1, 3, 6, and 12 months will be recorded.

In the event a subject is randomized but does not receive the trial interventions, the treatment will not be reassigned. Trial personnel will assess the patient and collect data throughout their enrollment in the trial. Participants in both arms will wear an actigraphy device (Appendix 1) to assess the quality and duration of sleep and activity for 1 week prior to the trial treatments (for collection of baseline data) and starting on the day of intervention for 1 month after to longitudinally assess the impact of the trial treatments on sleep and physical activity.

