### Participant timeline

Participants who meet the inclusion criteria will be reached by research coordinator for possible enrollment. Participants will be enrolled in the study after consenting and before receiving a RFN of the CMBN. The goal of this trial is to demonstrate non-inferiority of the end-on technique as compared to the conventional parallel technique for RFN of the CMBN. The baseline study questionnaires will be completed within 4 weeks before the study intervention. Baseline data on sleep and physical activity will also be collected using actigraphy over 1 week prior to the trial intervention and for at least 1 week prior to the follow-up at 1 month after the intervention. Routine scheduled study follow-ups will occur at 1, 3, 6, and 12 months after the study interventions, at which times all follow-up measures will be obtained (Table 2, Fig. 1). The follow-up at 1 and 3 months will be in-person whereas the follow-ups at 6 and 12 months may be virtual (video/phone) to assess trial-relevant outcomes.

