### Actigraphy monitoring

This is a non-invasive method to assess sleep and activity. An accelerometer-based wrist-worn device (GENEActiv®, Activeinsights, Cambridge, UK) records activity, light and temperature continuously for up to one month. The unprocessed , accessible in an open data format, can be analyzed using specific algorithms.

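### The actigraph is worn for a month from the procedure to follow sleep and activity over time, but the defined outcome has one post-treatment window, the week before the 1-month visit

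*Protocol article*

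**What the plan says.** The protocol article describes actigraphy in several places, and they do not agree on how long it is worn or which days are analysed.

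- **Post-procedural management:** one week of wear before treatment for baseline data, then wear "starting on the day of intervention for 1 month after to longitudinally assess the impact of the trial treatments on sleep and physical activity".
- **Participant timeline:** a baseline week, then wear "for at least 1 week prior to the follow-up at 1 month after the intervention".
- **Objectives:** average activity and sleep duration "over 1 week before the procedure and 1-month follow-up after the study interventions". This does not settle whether the later window is a week or the whole month.
- **Outcomes, actigraphy item:** the between-group difference in average activity and sleep duration "over 1 week prior to the procedure and 1 week prior to the 1-month follow-up after the interventions".
- **Outcomes, sleep and quality-of-life item:** "actigraphy-measured variables respectively, including sleep duration, sleep quality, daytime sleepiness, sleep timing, and wakefulness after sleep onset". No actigraphy window is given for these variables.
- **Table 2:** sleep duration and activity from the device are marked at baseline and 1 month only.
- **Appendix 1:** the device "records activity, light and temperature continuously for up to one month".

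On what might differ early, the Abstract says that the end-on approach "may be technically easier and require less time while reducing post-procedural discomfort". The Sample size section likewise mentions possibly fewer adverse effects, with patient discomfort as an example. For the parallel technique, the Background states that "only the rates of post-procedural pain seem to be relatively concordant between authors, with reported rates varying between 95 and 100" per cent.

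**The concern.** A month of continuous wear with a declared longitudinal purpose needs at least one outcome that uses the course over that month. The only actigraphy outcome with a defined window uses the last week. Roughly the first three weeks are to be recorded under one section, need not be recorded under another, and feed no windowed outcome.

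Those weeks matter to the trial's own argument. Non-inferiority is justified by similar efficacy together with a possible gain in discomfort and resource use. Any gain in post-procedural discomfort would be felt soon after the procedure, where the other measures are sparse. In Table 2, NRS is taken immediately after the procedure and next at 1 month. The opioid outcome averages only the week before each visit. Adverse effects are marked at 1 month, and the Safety section says they come from open-ended questions. The actigraph would be the one objective, continuous record of early recovery. Without a defined outcome, any early finding from it would be post hoc.

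A smaller point concerns the wording. The actigraphy item lists the pre-procedure week alongside the later week as something to be compared between groups. Randomization takes place on the procedure day, so a difference in that week cannot be a treatment effect.

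**Working it through.** The protocol gives no figure for this outcome, so there is none to reproduce. The check is a comparison of sections, a count of days, and an illustration of what baseline adjustment gains.

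**1. Wear period against analysis window**

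| Section | Post-procedure wear or data | Window analysed |
|---|---|---|
| Post-procedural management | procedure day to 1 month | none stated; longitudinal aim |
| Participant timeline | at least the week before the 1-month visit | none stated |
| Objectives | not stated | ambiguous |
| Outcomes, actigraphy item | not stated | week before the 1-month visit |
| Outcomes, sleep item | not stated | none |
| Table 2 | 1-month column only | none stated |

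The Follow-up data section adds a further inconsistency: it lists actigraphy among the data collected at 1, 3, 6 and 12 months, whereas Table 2 stops at 1 month.

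The one longitudinal model named under Statistical methods relates pain reduction to improvement in function, using changes from baseline to 3, 6 and 12 months. It does not cover the first month and does not mention actigraphy.

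**2. Share of the wear period with a defined window**

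Assumption: one month is 28 to 31 days. Days used = 7; days without a window = d − 7; share = (d − 7)/d.

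- d = 28: 21 days, 21/28 = 75.0%
- d = 30: 23 days, 23/30 = 76.7%
- d = 31: 24 days, 24/31 = 77.4%

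This applies if participants wear the device for the full month. If sites collect only the one-week minimum, the early days are not recorded at all.

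**3. Recording length**

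A baseline week plus a month is 35 to 38 days (7 + 28 to 7 + 31). Appendix 1 gives up to one month of continuous recording. This is no contradiction if the baseline and follow-up periods are recorded separately, but the procedure should say so.

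**4. What baseline adjustment gains (illustrative)**

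With 36 per arm, two-sided 0.05 and 80% power, the smallest detectable difference in a weekly average is about 0.67 SD unadjusted. With the pre-procedure week as a covariate it is multiplied by √(1 − r²), where r is the correlation between the two weeks. The documents do not give r, so a range is assumed:

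- r = 0.6: 0.67 × 0.800 = 0.54 SD
- r = 0.7: 0.67 × 0.714 = 0.48 SD
- r = 0.8: 0.67 × 0.600 = 0.40 SD

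The adjustment uses only data already planned.

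**The case against.** The strongest reply is that the article states a longitudinal aim, lists some actigraphy variables without a window, and may leave epochs and modelling of wearable data to a full protocol or analysis plan that is not shown. That stands in part. It would be wrong to say that the early data will not be compared; what can be said is that the article defines no outcome for them. But the article does fix the window of its actigraphy outcome, and that window does not serve the purpose stated for the month of wear.

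Second, a one-week minimum does not strictly conflict with a month of wear, since a month satisfies it. That is correct as logic. In practice, a site working from the Participant timeline could comply with it and still miss what Post-procedural management asks for.

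Third, the chosen week is defensible. It matches the opioid averaging window and the 1-month questionnaires, and it avoids the first days, when sedation and as-needed opioids could affect movement and sleep. This stands, and is a reason to keep the window and add to it.

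Fourth, the pre-procedure week is labelled baseline elsewhere and in Table 2. The intent is probably sound, and only the wording of the outcome needs correction.

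A reader might also infer that the arms are expected to differ in early activity or sleep, and that the present outcome will miss it. The documents do not support this. They raise only a possible difference in discomfort and adverse effects; the stated hypothesis for sleep is non-inferiority; the 95 to 100% figure is for the parallel technique alone; and no duration of post-procedural pain is given.

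**Conclusion.** The point holds as a mismatch between data collection and outcome definition in one secondary domain. About three quarters of the planned post-procedure wear (21 to 24 of 28 to 31 days) has no outcome with a defined window, and the sections disagree on whether those days must be recorded. The count rests on full wear and on the assumed length of a month.

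It does not support a claim about lost power. One could posit a 0.67 SD difference in week 1 that has vanished by week 4, and contrast 80% power in week 1 with a 5% rejection rate in week 4. Both figures are true by construction, because 0.67 SD is the difference detectable with 80% power and the week-4 difference is set to zero. They say nothing about this trial.

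The matter is worth correcting because the correction is cheap and serves the protocol's own longitudinal aim.

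**What to change.** 1. In the actigraphy outcome, keep the average over the week before the 1-month visit as the between-group comparison. Use the pre-procedure week as a covariate, not as a compared window.
2. Add weekly averages of activity and sleep duration for weeks 1 to 3. Analyse all post-procedure weeks in a repeated-measures model with arm, week, their interaction and the baseline week. Name the week-1 contrast in advance as a supportive early-recovery measure.
3. Give the further actigraphy sleep variables a window, or state that they follow the same scheme.
4. Bring the Objectives, Outcomes and Participant timeline into line with the wear period in Post-procedural management. Reconcile the Follow-up data section with Table 2, and say how the baseline and follow-up recordings fit the device's one-month capacity.
5. Define a valid day and the minimum number of valid days per week.

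The cost is wording, some extra analysis and one more contrast in an already long secondary list. There are no added visits, and no wear beyond what Post-procedural management already asks. For sites that have used the one-week minimum, wear from the procedure day would be an added burden. Recruitment began in March 2023, so early data may be missing for participants already treated on that basis; the number with usable week-1 data should be reported by arm.
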